## Abstract

**Background:**

Low back pain is highly prevalent and a significant public health burden in Western society. Feasibility studies suggest personalised pedometer-driven walking is an acceptable and effective motivating tool in the management of chronic low back pain (CLBP ≥ 12 weeks). The proposed study will investigate pedometer-driven walking as a low cost, easily accessible, and sustainable means of physical activity to improve disability and clinical outcomes for people with CLBP in Saskatchewan, Canada.

**Methods/design:**

A fully-powered single-blinded randomised controlled trial will compare back care advice and education with back care advice and education followed by a 12-week pedometer-driven walking programme in adults with CLBP. Adults with self-reported CLBP will be recruited from the community and screened for elibility. Two-hundred participants will be randomly allocated to one of two intervention groups. All participants will receive a single back care advice and education session with a physiotherapist. Participants in the walking group will also receive a physiotherapist-facilitated pedometer based walking programme. The physiotherapist will facilitate the participant to monitor and progress the walking programme, by phone, on a weekly basis over 10 weeks following two face-to-face sessions. Outcome measures of self-reported disability, physical activity, participants’ low back pain beliefs/perceptions, quality of life and direct/indirect cost estimates will be gathered at baseline, three months, six months, and 12 months by a different physiotherapist blinded to group allocation. Following intervention, focus groups will be used to explore participants’ thoughts and experiences of pedometer-driven walking as a management tool for CLBP.

**Discussion:**

This paper describes the design of a community-based RCT to determine the effectiveness of a pedometer-driven walking programme in the management of CLBP.

**Trial registration:**

United States National Institutes of Health Clinical Trails registry (http://ClinicalTrails.gov/) No. NCT02284958. Registered on 27^th^ October 2014).

## Background

Chronic low back pain (CLBP) – back pain present for greater than three months [1] – is a prevalent, disabling, and costly musculoskeletal disorder in need of effective, efficient, and accessible interventions [2]. Low back pain (LBP) is a substantial public health burden in western society [3]. In Canada, the cost of medical expenditure for low back pain is estimated at up to $12 billion annually with additional costs linked to loss in worker productivity, lost work time, and associated disability payments [4,5]. Although research describes an episode of acute LBP as predominantly self-limiting [6], it is also known to be the most significant predictor of CLBP [7,8]. Four out of five Canadians will experience at least one episode of LBP at some point in their life and one in five adult Canadians will report the presence of CLBP at any given time [9].

CLBP is also significantly associated with a range of psychological and physical comorbidities and lower socioeconomic status [10]. Being overweight or obese increases the risk of LBP, and has the strongest association with seeking care for CLBP [11]. In contrast, reduction in weight improves outcomes for patients with musculoskeletal disorders [12]. Although the relationship between weight and physical activity is mediated by a variety of factors, the modern Canadian lifestyle is more sedentary with many people working in seated positions and a greater use of vehicles for transportation [13]. It has been posited that work pressure and other priorities create a perception of less time to undertake fundamental physical activities, such as walking, that are known to offer substantial health benefits [13]. A recent systematic review and meta-analysis shows the positive effect of walking, a basic human activity, on chronic musculoskeletal pain and self-reported disability [14].

Much attention has been devoted to interventions and strategies for managing CLBP; however, effective management remains elusive [15,16]. Interestingly, although walking is recognised as a fundamental human activity, there is limited literature on its use as an intervention strategy for CLBP [14,17-21]. Further research is required to determine the effectiveness of walking programmes as an intervention for CLBP and, subsequently, to develop guidelines on how to implement such programmes. Encouraging people with CLBP to increase physical activity through walking, however, can be problematic due to fear of pain exacerbation [6]. A systematic review suggests there is strong evidence to using pedometer-based walking interventions to increase physical activity and enhance quality of life in people with musculoskeletal disorders [22]. Researchers in the United Kingdom have recently completed a feasibility study of a community-based, pedometer-driven clinician guided walking programme for CLBP and found high levels of patient satisfaction and adherence, increased walking, improved physical function, reduced disability, and reduced pain, all demonstrating support for more definitive clinical trials [21].

Saskatchewan is a Canadian province with approximately 30% of the population residing in rural communities in which agriculture is a key industry [23]. Prevalence data for LBP in Saskatchewan shows point and lifetime prevalence at 28% and 84% and low to high disability CLBP ranging from 49% to 11% respectively [24]. People living in rural and remote areas of Saskatchewan are more likely to be afflicted with low back disorders [10,25]. Farmers and rural workers are much more prone to LBP [26]. The physical demands of farming combined with the very long work hours during planting and harvesting [27] and physical exposures such as whole body vibration and heavy lifting present a uniquely vulnerable scenario [28,29]. Back problems impact negatively on farming productivity; influencing work activity and reducing farm income [30]. Although farming is considered to be a physically active occupation, reduced activity has been reported in those with chronic health conditions [31].

### Aim and objectives

The proposed study will investigate pedometer-driven walking as a low-cost, easily accessible, and sustainable means of physical activity to improve disability and clinical outcomes for people with CLBP in Saskatchewan, Canada. Our hypothesis is that individualised advice and education followed by a pedometer-driven walking programme will be a more clinically and cost-effective option for the management of CLBP compared to advice and education alone. Results from this study will inform future exercise-based strategies for larger comparative international clinical trials aimed at reducing disability in those suffering from CLBP. The study’s objectives are fourfold:To determine perceived levels of disability and baseline levels of walking activity in a sample of Saskatchewan residents with CLBP.To determine the uptake and adherence to a pedometer-driven walking programme for people with CLBP.To test the difference in clinical and cost-effectiveness of a walking programme to improve outcomes for CLBP compared to an individualised back care education package.To test the feasibility of a walking programme in a sub-sample of rural Saskatchewan farmers/agricultural workers. Specifically, we will compare recruitment and adherence rates of farmers relative to non-farmers in light of the unique work demands, work and living environment in the rural community.

### Ethical approval

The study has been granted approval by the University of Saskatchewan Biomedical Ethics Board (#14-218) and registered with the United States National Institutes of Health Clinical Trails registry (https://clinicaltrials.gov No. NCT02284958). Written informed consent from all participants will be required prior to entering the study.

### Description and selection criteria of participants

A pragmatic, community-based approach will be used to recruit adults with CLBP residing in urban and rural communities within the boundaries of the Saskatoon Health Region, Saskatchewan, Canada. A wide variety of recruitment strategies such as posters, fliers, clinical and public notice boards, newspapers, and electronic bulletin boards will be used to ensure a mixed group of people representative of the CLBP population. People under active treatment by a health professional will be eligible to take part, as will those currently receiving no clinical intervention. Programme intake will be ongoing as participants are recruited from the community over time. We expect to complete full recruitment by 15 months and complete the full 12-month follow up by 27 months.

In order to address the higher prevalence and risk for CLBP among the rural farming workforce, we will specifically recruit a minimum of 20 participants with CLBP who live in the rural community and work on farms geographically located within the Saskatoon Health Region. These 20 participants will be part of the full recruitment strategy for random allocation and, thus, will also provide a subgroup for investigation of intervention feasibility within this unique vulnerable population.

### Screening

Study inclusion and exclusion criteria are presented in Table 1. Potential participants will be screened for eligibility over three stages: 1) by a research assistant over the phone; 2) by a physiotherapist following clinical examination and; 3) following a pedometer trial.

**Table 1 Tab1:** **Inclusion and exclusion criteria**

**Inclusion criteria**	**Exclusion criteria**
Males and females aged 18 years or over	Any spinal surgery in the past 12 months
LBP (i.e. between the 12th costal margin and gluteal fold with or without associated leg pain) persisting for a minimum of three months	Evidence of nerve root, spinal cord, or cauda equina compression assessed by a physiotherapist
Physically able to participate in a walking programme as determined by the PAR-Q*	Current lower extremity musculoskeletal injury, cardiorespiratory or other medical condition that may be a contraindication to increasing physical activity levels
Average daily walking is fewer than 7500 steps as determined by a one week pedometer trial	History of serious psychological or psychiatric illness
	Current pregnancy
	Average daily walking is greater than 7500 steps as determined by a one week pedometer trial

*PAR-Q – Physical Activity readiness Questionnaire (Shephard 1988). If a participant answers yes to one or more questions on the PAR-Q, they will be advised to consult their primary healthcare provider to obtain physical clearance prior to confirming study participation.

#### Pedometer trial

Individuals deemed clinically suitable for the study will be invited to wear a sealed pedometer for seven days in order to establish a baseline measurement of steps [20]. Although there has been little research on step count thresholds for inclusion in a CLBP study, previous research and review by Tudor-Locke and colleagues [33,34] has identified ~7,500 steps as a baseline cut-off for interventions relative to health improvement. Therefore, only potential participants who walk less than an average 7,500 steps per day, over the seven day trial, will be invited to take part in the full study.

### Outcome measures

All eligible participants will meet with a blinded assessor (a different physiotherapist from the research team) to complete a battery of questionnaires. Measures will be taken at four time points; baseline, three months (or, for the walking group, immediately following intervention), six months and 12 months.

#### Primary outcome

##### Self-reported functional disability

The Modified Oswestry Low Back Pain Disability Questionnaire (ODQ), a valid and reliable measure of pain and physical function in LBP patients, will be used as the primary outcome measure [35]. Ten questions, each with six options, assess an individuals’ perceived activity restrictions in daily tasks. A minimum score of zero and a maximum score of five is allocated to each question and summed. The recent UK *feasibility* study (n = 57) of pedometer-driven walking in people with CLBP demonstrated a 6 to 7 point between group difference at six months and will be used as a comparator in this study [21].

#### Secondary outcomes

##### Physical activity level (PA)

Participants will complete the International Physical Activity Questionnaire short form (IPAQ) at each time point. The IPAQ is a well-established tool for assessing PA and is considered valid and reliable for assessing PA levels in clinical populations [36-39]. The IPAQ uses seven questions asking participants about the time they spent being physically active in the last seven days.

##### Participant beliefs/perceptions

The Fear-Avoidance Beliefs Questionnaire (FABQ) will be used to assess participants’ perceptions about how PA and work affects their CLBP [40]. The FABQ is a 16 item self-report questionnaire divided into two sub-scales with established reliability and validity in individuals with persistent pain conditions; PA (five questions) and work (11 questions). Participants rate each question on a scale from zero to six, were zero indicates complete disagreement with the statement and six indicates complete agreement. Four scores from the PA sub-scale and seven from the work sub-scale are summed giving maximum scores of 24 and 42 respectively.

Individuals’ beliefs regarding their future living with CLBP will be assessed using the Back Beliefs Questionnaire (BBQ). Individuals rate their level of agreement with 14 statements on a scale from one to five were one indicates complete disagreement and five indicates complete agreement. Five statements are considered ‘distractors’ and not used in scoring. Each statement score is reversed so that low scores represent negative beliefs and then summed to determine the final score. The BBQ has been found to have good validity (Cronbach’s Alpha = 0.70 to 0.75) and reliability (Intraclass Correlation Coefficient = 0.87) [41,42].

At baseline, participants will be asked to rate their ability to be more physically active compared to the previous week using the Global Rating of Change for Physical Activity questionnaire [43,44]. Participant ratings will be recorded as no change, worse, or better. If they answer worse or better, they will be asked to quantify the amount using one of the following markers: a tiny bit - almost the same; a little bit; somewhat; moderately; quite a bit, a great deal or a very great deal. Participants will also be asked to rate how important this change (or lack of change) is to them using the same markers. At each follow up assessment, participants will be asked to give a rating compared to the last time point.

##### Quality of life

Back pain significantly impacts quality of life [45]. Our study will use Quality Adjusted Life Years (QALYs) to estimate the impact of a walking programme on an individual’s quality of life. The EuroQol health survey instrument (EQ-5D-5 L) [46] is a self-administered survey tool that captures general health status. Participants rate their health on the day of testing over five domains (mobility, self-care, usual activities, pain/discomfort, and anxiety/depression) on a five-point scale and then score on a scale of 0 to 100 how their health today compares to their best (100) or worst (zero) health ‘imaginable’. An individual’s rating of each of the five health-related domains is summarised as a single score in the form of a utility estimate. The utility estimate will then be converted into a QALY for each participant and an average QALY for each group. We will compare the difference in QALYs at three, six, and 12 months.

##### Cost assessment

Direct and indirect healthcare-related costs associated with both intervention groups will be collected using a combination of patient diaries and questionnaires at each testing session throughout the 12 month study period. At baseline and each follow up visit, information will be collected regarding healthcare utilisation over the preceding 3-month period, including physiotherapy, family physician, and walk-in clinic visits, emergency room visits, and hospitalisations. Work status, work efficiency, time lost from unpaid work and absenteeism will be measured in each group using the Work Productivity and Activity Impairment questionnaire [47]. The difference in total costs will be compared at three, six, and 12 months.

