### Randomisation

A computer generated random sequence will be performed using minimisation allocation with a 1:2 ratio to the back care advice and education group or back care advice and education plus pedometer-driven walking group [48]. To ensure adequate access to pedometers, randomised sequences will be created in blocks of 30 at a time (20 treatment: 10 control) and each allocation placed in a sealed blank envelop. As the self-management nature precludes double blinding, only the assessor for outcome measurements will be blinded to group allocation.

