### Sample size

Given the non-invasive nature of a walking intervention likely carrying minimal health risk, we have chosen to use a 1:2 allocation ratio towards the walking intervention in order to increase confidence in interpreting or accepting any observed effect [58,59]. Results from the feasibility study informed initial calculations of sample size based on between group differences of 6–7 points in the ODQ. Given the wide confidence intervals expressed in these between group feasibility data and consdiering the recommended minimum important change of 10–12 points for individual improvement [60], we chose to first explore for an eight point between group difference. An 80% power calculation (alpha = 0.05), resulted in a minimum requirement of 174 participants (116 walking group, 58 standardised group). We anticipate a 15% loss to follow-up and will thus, aim to recruit 200 participants.

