### Statistical analysis

Multiple regression and/or mixed model analyses will be used to determine predictive models that best test for differences and changes in both outcomes and costs. Both within- and between group models will be used in order to determine whether use of a pedometer in the manner described in this study is a predictor of these outcomes. The change in ODQ from baseline will be the main dependent variable. Other outcome measures will be entered as alternate dependent variables to determine whether they significantly alter or provide a stronger model. Personal, occupational, seasonal, clinical and anthropometric variables will be entered into the model in a stepwise manner to seek the models that best explain changes in outcomes. Descriptive and statistical results for personal, demographic, anthropometric and outcome measures will be presented in tabular and graphic format.

Focus group discussions will be audio-recorded, transcribed and imported into NVivo 10 (QSR International) software for analysis. Thematic analysis using inductive methods will be used to identify core ideas important to participants’ experience, meaning and reality of pedometer-driven walking [61].

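### The cost comparison does not fix the already collected 3-month pre-baseline healthcare use as a covariate, and stepwise selection does not guarantee that it enters

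*Protocol article*

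**What the plan says.** The Cost assessment section sets out both the data and the contrast. On the data: "At baseline and each follow up visit, information will be collected regarding healthcare utilisation over the preceding 3-month period". On the contrast: "The difference in total costs will be compared at three, six, and 12 months". It names no adjustment and does not define the period that a total covers at each time point.

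The Statistical analysis section is the only other text on how costs are analysed. It plans multiple regression and/or mixed models to find "predictive models that best test for differences and changes in both outcomes and costs". Its covariate rule is that "Personal, occupational, seasonal, clinical and anthropometric variables will be entered into the model in a stepwise manner". Neither baseline cost nor prior healthcare use is named. For the form of the dependent variable, only the disability score is settled: "The change in ODQ from baseline will be the main dependent variable". For the rest, "Other outcome measures will be entered as alternate dependent variables", without saying whether as a level or as a change.

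Cost-effectiveness is part of the hypothesis and of the third objective (Aim and objectives).

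**The concern.** A participant's earlier healthcare use is a natural predictor of later healthcare cost, and here it is collected from everyone. Using it in the comparison costs nothing and can only be relied on if the model is told to include it. The stated covariate rule does not do that. Even if prior use is counted among the clinical variables, it stays only if the stepwise search keeps it. The search is also described as serving the explanation of changes in outcomes, so its application to costs is not certain.

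Three features of the trial make this worth a sentence in the plan:

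- The eligibility text admits people under active treatment as well as people receiving none, so prior use should vary widely.
- The Randomisation section specifies "minimisation allocation with a 1:2 ratio to the back care advice and education group" but names no balancing factor, so nothing stated in the article balances the arms on prior use.
- The control arm is planned at only 58 evaluable participants.

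At stake is the width of the confidence interval for the cost difference, and how far a chance difference in prior use carries into the point estimate.

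**Working it through.** **Inputs.** The arm sizes, 116 walking and 58 control, come from the Sample size section, where they were derived for the disability score ("we chose to first explore for an eight point between group difference"). The article gives no standard deviation, power or sample size for costs, so there is no cost figure to reproduce. It also gives no correlation r between baseline and follow-up cost; r = 0.2 to 0.6 is assumed below.

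**Step 1: size of chance imbalance.** In units of the baseline SD, the standard error of the baseline difference between arms is √(1/116 + 1/58) = √0.02586 = 0.161. About 1 trial in 20 has an imbalance of at least 1.96 × 0.161 = 0.315 SD.

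**Step 2: relative variance of the estimated cost difference.** Assume a linear relation, a common slope and equal variances in the two arms.

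- Follow-up cost without adjustment: 1
- Change from baseline, with equal baseline and follow-up SD: 2(1 − r)
- Follow-up cost adjusted for baseline: 1 − r²

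**Step 3: carry-over of an imbalance.** An imbalance of d baseline SDs shifts the unadjusted difference by r × d and the change-score difference by (r − 1) × d, in SDs. Adjustment removes the expected shift under the linear model.

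| Assumed r | Variance, change | Variance, adjusted | Reduction against none | SE, adjusted (none: 0.161 SD) | Unadjusted shift, d = 0.161 | Unadjusted shift, d = 0.315 |
|---|---|---|---|---|---|---|
| 0.2 | 1.60 | 0.96 | 4% | 0.158 | 0.032 SD | 0.063 SD |
| 0.3 | 1.40 | 0.91 | 9% | 0.153 | 0.048 SD | 0.095 SD |
| 0.5 | 1.00 | 0.75 | 25% | 0.139 | 0.080 SD | 0.158 SD |
| 0.6 | 0.80 | 0.64 | 36% | 0.129 | 0.096 SD | 0.189 SD |

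The interval narrows by 1 − √(1 − r²), which is about 2%, 5%, 13% and 20%.

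**Step 4: if the time windows differ.** Suppose the baseline covers three months and the total covers more, and let k be the baseline SD divided by the follow-up SD. The relative variance of total minus baseline is 1 + k² − 2rk. The adjusted variance is still 1 − r². The gap is (1 + k² − 2rk) − (1 − r²) = (k − r)², which is never negative. So adjustment is at least as precise as subtraction whatever the windows, and it does not need them to match. The gap can be small: with k = 0.5 (assumed) and r = 0.3, subtraction gives 1 + 0.25 − 0.30 = 0.95 against 0.91.

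**The case against.** A reader might infer that costs will be compared as raw, unadjusted differences. The article does not say so. Its sentence on costs names a contrast and time points, and an adjusted difference is still a difference in total costs. The Statistical analysis section plans regression or mixed models with covariates, prior use could enter among the clinical variables, and a mixed model could include the baseline value.

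A reader might also infer that costs will be analysed as change scores, or that a three-month baseline will be subtracted from a 12-month total. Only the disability score is expressly a change, and the total's window is undefined. Each visit asks about the preceding three months, so a like-for-like comparison per window is possible.

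Nor do the documents support a claim of systematic bias. Under random allocation, chance imbalance is already reflected in the ordinary confidence interval.

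The size of the gain is also open. The baseline item is use of services, not a full cost, whereas follow-up totals include indirect costs over an undefined period. The correlation may be modest, and at 0.2 the gain is slight. Finally, this is a condensed article, and an analysis plan may name the covariate.

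All of this limits the wording and the severity. What remains is that the article is not silent on covariates: it states a rule, stepwise entry, and that rule does not secure the adjustment.

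**Conclusion.** The point holds as a minor one. The cost comparison does not prespecify prior healthcare use as a covariate, although it is collected, and the stated stepwise rule leaves its inclusion to chance.

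The gain from fixing it is in precision, a variance reduction of about 4% to 36% over assumed correlations of 0.2 to 0.6, and in protection against chance imbalance. At a typical one-standard-error imbalance, the unadjusted difference would move by 0.03 to 0.10 SD over that range. The larger shifts in the last column of the table belong to the 1-in-20 case.

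These figures rest on an assumed correlation, a linear model with equal variances and a common slope in the two arms, and the 116 and 58 planned for the disability score. Skewed costs would change the amounts. Nothing here shows that the cost result would be invalid.

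**What to change.** Add to Cost assessment and Statistical analysis that, at each horizon, total cost (not its change) is the dependent variable. Arms are compared by regression with the participant's costed healthcare use in the three months before baseline as a fixed covariate, held outside the stepwise search. State that the same adjusted difference enters the cost-effectiveness estimate, and define the period that each total covers.

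This takes a sentence or two of analysis wording. The baseline data are already collected, so no further data, visits or participants are needed. Baseline use must be costed with the same unit costs as follow-up use. The only downside is that a rule is needed for participants with missing baseline use, and it should be written down in advance.
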